## **Methods**

**Study design:** The proposed project is a prospective, single blind, randomized controlled intervention trial in patients with chronic stroke.

**Setting:** Patients will be recruited from the Rehabilitation Center Paramaribo; from the community and from the union for people after stroke.

**Patient population:** Patients with chronic ischemic stroke and following the inclusion criteria can be included in the study:

Inclusion criteria:

- ability to give informed consent
- ability to understand measurement procedures defined as MMSE >24 [22]
- last stroke >6 months ago
  
- mild to moderate stroke deficit defined by Fugl Meyer test score of 27 to 90 for upper and lower extremities [12]
- FAC  $\geq 3$
- medical clearance to participate in a moderate exercise program
- living at home and having a minimum of 5 stairs at home

Exclusion criteria:

- serious cardiac condition [22]
- other serious end organ damage
- other neurological deficits leading to disability
- uncontrolled blood pressure (systolic pressure >140, diastolic pressure >90) [22]

**Statistical power and sample size:** Sample size calculation was performed with PS Power and Sample Size Calculation (<http://biostat.mc.vanderbilt.edu/PowerSampleSize>) The sample size for the two-sample case (training versus control) was estimated on the basis of the results of Moore et al [13] for effect of exercise on cardiorespiratory capacity. In this study the response for peak VO2 within each subject group was normally distributed with standard deviation 3.4. If the true difference in the experimental and control means is 3.0, we will need to study 17 experimental subjects and 17 control subjects to be able to reject the null hypothesis that the

population means of the experimental and control groups are equal with probability (power) 0.8. The Type I error probability associated with this test of this null hypothesis is 0.05. We chose to aim for a sample size of 20 patients per group taking drop outs into account.

Participant stratification will be balanced for gender because men tend to have higher aerobic capacity and muscle strength than women. The participants will be assigned randomly to a group by a computer program ([www.randomization.com](http://www.randomization.com)). Informed consent (appendix I) must be signed by every participant.

**Intervention** There is an intervention group (physical fitness exercise) and a control group (usual care) [13].

The intervention employs a holistic approach bringing together physical fitness improving exercises and upper limb exercises. The intervention is adapted from earlier studies in which physical fitness exercise showed a positive effect on cardiorespiratory capacity [12, 13] in chronic stroke survivors, along with earlier research experience on upper limb rehabilitation for stroke survivors [19]

The core of the exercise program will consist of three main exercises: stair climbing, chair rises [12] (is considered a balance exercise also) and walking [13].

At this moment Suriname does not have a structural exercise program in place for chronic stroke survivors. For this reason the usual care will exist of no exercise.

*Table 1. Overview Intervention Group activities*

| Intervention group |                                                                                                                                                                                                                                                                                                                                                                                                                                   |                                                                                                                                                                                                                                                |
|--------------------|-----------------------------------------------------------------------------------------------------------------------------------------------------------------------------------------------------------------------------------------------------------------------------------------------------------------------------------------------------------------------------------------------------------------------------------|------------------------------------------------------------------------------------------------------------------------------------------------------------------------------------------------------------------------------------------------|
| 15 min             | Warming up                                                                                                                                                                                                                                                                                                                                                                                                                        | Hip circles
Knee circles
Ankle circles
Slow marching
Stretching (gluteus, quadriceps femoris, hamstrings, triceps surae)
Shoulder circles
Shoulder abduction/adduction
Elbow extension/flexion
Wrist extension/flexion |
| 40 min             | Functional strengthening lower limbs
[increase intensity gradually after first 5 minutes of exercise with perceived exertion 4-5 out of 10 on BORG scale]

[start with 2 sets of 5 and gradually increase to 3 sets of 10 with variable speed]

[use amount of steps as target and gradually increase to more to complete in certain time limit in which perceived exertion should be 4-5 out of 10 on BORG scale] | Stair climbing

Sit-to-stand

Walking                                                                                                                                                                                              |
| 15 min             | Cooling down (combination stretch exercise upper and lower limb)                                                                                                                                                                                                                                                                                                                                                                  | Mobility exercise for upper and lower limb followed by slow stretching (upper extremity and the same muscle groups of lower limb)                                                                                                              |

The intervention will be provided by a physical therapist for 4 weeks (3 times/wk, 70 minutes). This duration of intervention was selected because it improved the cardiorespiratory function of chronic stroke survivors [11]. After that a telephone supervised method for 4 weeks is done to monitor if the patient is continuing the exercise program at a given intensity. To progress in cardiorespiratory fitness level a pedometer based step goal [4] will be set.

**Measurements:** Following measurements and paper and pencil surveys will be undertaken in order to evaluate the subjects at baseline at 4 weeks, 8 weeks and 5 months:

**Anthropometric characteristics** weight, height, body mass index, % fat (bio-electrical impedance) and waist and hip circumference will be measured.

**Exercise tolerance** (peak VO2) will be assessed by submaximal graded cardiopulmonary exercise testing (CPET) with breath-by-breath analysis (Jaeger Oxycon Mobile®) on a cycle ergometer. Submaximal fitness parameters will include 1st and 2nd ventilatory thresholds, oxygen uptake efficiency slope and the VE/VCO2-slope. We will use a graded protocol in which the patient starts with a 10 min warming-up session at zero workload [12] followed by workload increments of 10W every minute until maximal effort is reached or symptoms appear [3, 12]. Submaximal effort is defined as the inability to continue cycling at a pace of 50-60 revolutions per minute due to shortness of breath and/or leg fatigue.

**Hemodynamic and vascular function at rest** will be non-invasively assessed by means of the Nexfin device which will provide resting systolic and diastolic blood pressure, cardiac output, stroke volume and systemic vascular resistance. Furthermore brachial ankle index will be determined by blood pressure measurements at non-paretic upper arm and ankle. Finally arterial stiffness will be evaluated by use of the Arteriograph.

**Lung function** will be evaluated by vital capacity and forced expiratory volume in 1 second measured before starting the CPET, using the same equipment for breath by breath analysis.

**Habitual physical activity** will be objectively assessed during 7 consecutive days and nights by means of the physical activity device that will also be used to guide the intervention, designed to be worn constantly around the upper arm (like a watch) [23].

**Walking endurance** will be tested with the 6-minute walk test. This test is a reliable submaximal test of cardiorespiratory capacity in people with stroke [24, 25].

**Quality of gait** will be defined by spatiotemporal parameters such as step length, stride length, step width, paretic stance time and gait speed. These parameters will be recorded in a human movement laboratory by two camera's (Panasonic HDC-TM900 3 MOS HD camcorder and Canon powershot SX40 HS) which capture data that will be analyzed with Kinovea, an open source video tool.

**The manual muscle testing (hand-held dynamometer), and handgrip strength test** will be used to evaluate upper limb function [26-29] and knee extensor strength [30, 31].

**Balance** will be evaluated by the Berg balance scale, which consists of 14 tasks and a score range of 0-56 [32].

**Health related quality of life** will be evaluated using the SF-12 questionnaire [33-35].

**Disabilities of arm, shoulder and hand** will be evaluated by means of the DASH questionnaire [36, 37].

**Exercise self-efficacy** will be evaluated by use of the Dutch translation of the Exercise Self-Efficacy Scale (ESES) [38].

**Database management** will be performed by use of Microsoft Excel 10.0. All data will be anonymized before being processed. Repeated measures ANOVA will be performed by use of SPSS statistical software in order to reveal differences between control and intervention groups regarding the primary and secondary outcome measures.

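### Entry clearance covers a moderate exercise program only, but every patient is due four graded cycle tests that run to maximal effort or symptoms under the label 'submaximal'

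*Protocol*

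**What the plan says.** Four parts of the Protocol's Methods bear on this point.

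- **Patient population, inclusion criteria.** The clearance required is "medical clearance to participate in a moderate exercise program". No other clearance is listed. The exclusions remove serious cardiac condition, other serious end organ damage, and blood pressure above 140 systolic or 90 diastolic.
- **Intervention, Table 1.** Training is held at a moderate level. For walking, "perceived exertion should be 4-5 out of 10 on BORG scale", and the same range is given for stair climbing. Controls receive no exercise.
- **Measurements, schedule.** The measurements are taken "in order to evaluate the subjects at baseline at 4 weeks, 8 weeks and 5 months", with no restriction by arm.
- **Measurements, Exercise tolerance.** Peak VO2 "will be assessed by submaximal graded cardiopulmonary exercise testing (CPET") on a cycle ergometer. After a warm-up at zero load the test proceeds, "followed by workload increments of 10W every minute until maximal effort is reached or symptoms appear". The text then adds: "Submaximal effort is defined as the inability to continue cycling at a pace of 50-60 revolutions per minute", because of breathlessness and/or tired legs.

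**The concern.** A clearance criterion should match the most demanding procedure a patient will undergo. Here it names the training, and the hardest procedure is the cycle test. A doctor might accept a patient for exercise at 4-5 out of 10 and yet not for a test that goes on until the patient cannot continue. If that patient has none of the listed exclusions, the criteria are met as written and the test is due at baseline, before any training.

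The wording adds to the difficulty. A clinician told that the test is submaximal could reasonably think that clearance for moderate exercise is enough. What is at stake is participant safety in a population that the Introduction describes as having low aerobic capacity and a raised risk of early death and recurrent stroke.

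**Working it through.** The Protocol states no figure on this point that could be reproduced. The main check is a comparison of text; the arithmetic prices the fix.

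**1. Level of clearance against level of exertion**

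| Item | Level stated | Who | When |
|---|---|---|---|
| Clearance at entry | Moderate exercise program | All patients | Entry |
| Training | 4-5 out of 10 | Intervention arm only | Weeks 1 to 8 |
| Graded cycle test | Maximal effort or symptoms | All patients | Baseline, 4 weeks, 8 weeks, 5 months |

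The clearance matches the training row and falls below the test row. The Exercise tolerance paragraph gives no ceiling on heart rate, workload or exertion short of the stated end points. That the cycle test is the hardest procedure is an inference, but a safe one: the other assessments are resting measures, lung function, a 6-minute walk, gait, strength, balance, activity monitoring and questionnaires. Controls never do the program that the clearance names, but they do take the test four times.

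**2. Uses of the word submaximal**

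- *Test label* (Exercise tolerance): conflicts with the stopping rule in the same paragraph.
- *Effort definition* (Exercise tolerance): describes inability to continue, which is a limit of effort and not a level below it.
- *"Submaximal fitness parameters will include"* (Exercise tolerance): introduces ventilatory thresholds and slopes; no conflict.
- *Walking endurance*: "This test is a reliable submaximal test of cardiorespiratory capacity in people with stroke", said of the 6-minute walk; no conflict.

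Two of the four uses need correction. Because the same word also describes a 6-minute walk, it does not tell the reader that the cycle test may go on to inability to continue.

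**3. What the fix could cost in power**

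Inputs from the Protocol's sample size paragraph: difference 3.0, SD 3.4, alpha 0.05, target 20 per group. I assume a two-sided, two-sample t-test. The noncentrality is (3.0/3.4)/√(1/n₁ + 1/n₂), with n₁ + n₂ − 2 degrees of freedom.

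| Patients | Noncentrality | df | Power |
|---|---|---|---|
| 20 + 20 | 2.790 | 38 | 77.6% |
| 20 + 19 | 2.754 | 37 | 76.5% |
| 19 + 19 | 2.720 | 36 | 75.4% |

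Loss per patient: (77.6 − 75.4)/2 = 1.1 percentage points. One patient is 1/40 = 2.5% of the target. The Protocol's own statement of 80% power at 17 per group is a separate matter and is not used here.

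**The case against.** The strongest reply is that the criterion is correct for what it names, and that nothing says it is the only medical check before the cycle test. The cardiac and blood pressure exclusions and the test procedure cite outside sources that may define further limits. The consent appendix is not available to read. Symptoms can end the test well before the patient is unable to continue, and how far it goes depends on how that rule is applied. The document gives no sign that any patient would be cleared for moderate exercise and refused the test.

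Much of this stands. A reader might infer that patients go unscreened into a maximal test, or that harm is to be expected. The documents do not support that: three relevant exclusions apply, symptoms stop the test, and no rate of harm can be derived. A reader might also infer that every test is driven to maximal effort; the text gives symptoms as an alternative end point.

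What does not stand is that these safeguards close the gap. The Protocol asks for clearance in addition to the exclusions, so it does not treat them as sufficient, and it sets that clearance below the test. The symptom stop acts once exertion is under way; it does not show that the patient was fit to start. The conflict between the label and the stopping rule lies within one paragraph and needs no outside source.

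**Conclusion.** The point holds as a mismatch in the level of clearance, made harder to see by a wrong label. It does not hold as a claim that screening is absent or that patients are known to be at risk. The group affected is narrow: patients with none of the exclusions whom a doctor would clear for moderate exercise but not for a symptom-limited test. Its size cannot be derived and may be zero.

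The conclusion rests on reading the stopping rule as written and on taking the cycle test as the hardest scheduled procedure. The power figures measure the possible cost of the fix, not the size of the defect. Priority is minor to moderate: the consequence is uncertain, and the correction is small.

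**What to change.** **Inclusion criteria.** Reword the clearance to: *medical clearance for a symptom-limited graded cycle test, repeated at four visits, and for a moderate exercise program*.

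**Exercise tolerance.** Change the test label from *submaximal* to *symptom-limited*. Begin the effort definition with *Maximal effort is defined as*. Keep the present stopping rule, so that symptoms still end the test early. The definition should not be reworded as the end of the test: stopping would then depend on being unable to keep the pace, and a patient with symptoms who could still pedal would not meet it.

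Leave the sentence on submaximal fitness parameters and the 6-minute walk wording unchanged. A preset stop below the patient's limit would also close the gap, but peak VO2 would then not be measured directly, so it is not preferred.

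**Cost.** One criterion and two phrases change; no visit or measurement is added. A few patients cleared only for moderate exercise may not enter, or may need work-up first. The Protocol does not say who would pay for that. Its Time Planning section promises patients no charges, so the research group would probably bear it. These patients fail before enrolment and can be replaced; the loss of about 1.1 percentage points of power per patient arises only if they are not.

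### The 17 per group has about 70% power, not 80%, under the two-sided test that the protocol implies; it reaches 80% only with an undeclared one-sided test or altered inputs

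*Protocol*

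**What the plan says.** The paragraph on statistical power and sample size (Protocol, Methods) sizes the trial on peak VO2 as a two-group comparison, using a published pilot trial of community exercise after stroke. It takes the response as "within each subject group was normally distributed with standard deviation 3.4" and continues: "If the true difference in the experimental and control means is 3.0, we will need to study 17 experimental subjects and 17 control subjects". The hypothesis to be rejected is that the "population means of the experimental and control groups are equal with probability (power) 0.8". On the error rate it says: "The Type I error probability associated with this test of this null hypothesis is 0.05". Drop-outs are covered in one sentence: "We chose to aim for a sample size of 20 patients per group taking drop outs into account". No drop-out rate is given.

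The paragraph does not say whether the 0.05 is one- or two-sided. The only analysis described, at the end of the Methods under database management, is a repeated measures ANOVA looking for differences between the groups. It names no direction, and no one-sided test is mentioned anywhere in the Protocol.

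**The concern.** A standardised difference of 3.0/3.4 = 0.88 usually needs slightly more than 20 per group for 80% power at two-sided 0.05, so 17 looks too small. This is the Protocol's only sample-size justification, and it concerns peak VO2, the measure of the aerobic capacity named first in the main objective. If the test is two-sided, the Type II error with 17 evaluable per group is about 30% rather than the stated 20%. The 20 per group, presented as a margin for drop-outs, would then fall short of 80% even if nobody dropped out.

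**Working it through.** **Inputs, all from the sample-size paragraph.** Difference d = 3.0; within-group SD s = 3.4; α = 0.05; power 0.80; two independent groups of equal size n. Sidedness is not given, so both cases are run.

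**1. Reproducing the 17.**

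One-sided 0.05, normal approximation: n = 2 × (1.645 + 0.842)² × (3.4/3.0)² = 15.9, so 16. The exact t-test (noncentral t, 2n − 2 degrees of freedom) has power 0.786 at n = 16 and 0.809 at n = 17, so it needs 17. The stated figure is reproduced.

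**2. The same inputs, two-sided 0.05.**

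Normal approximation: n = 2 × (1.960 + 0.842)² × (3.4/3.0)² = 20.16, so 21. The exact t-test has power 0.797 at n = 21 and 0.816 at n = 22, so it needs 22. The stated 17 is 4 or 5 per group lower, which is more than rounding or choice of formula explains.

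**3. Power at the stated sizes.** The noncentrality parameter is d / (s × √(2/n)): 2.572 at n = 17 and 2.790 at n = 20.

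| n per group | Two-sided, exact t | Two-sided, normal approx. | One-sided, exact t |
|---|---|---|---|
| 17 | 0.704 | 0.730 | 0.809 |
| 20 | 0.776 | 0.797 | 0.863 |
| 22 | 0.816 | 0.833 | 0.891 |

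The two-sided Type II error at 17 per group is 1 − 0.704 = 0.296, about 1.5 times the stated 0.20.

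**4. Difference detectable with 80% power (two-sided, exact t, SD 3.4).** 3.37 with 17 per group; 3.09 with 20 per group.

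**5. Changed inputs that also give 17, two-sided.** If the SD and the difference are equal (3.0 and 3.0, or 3.4 and 3.4), the exact t-test needs 17, with power 0.807. If the power target is lowered to 0.70, the stated SD and difference also give 17. The paragraph states none of these.

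**6. Effect of baseline adjustment (assumption only; the Protocol gives no correlation).** If 3.4 is the SD of the outcome value and r is the baseline–outcome correlation, the residual SD is 3.4 × √(1 − r²), with 2n − 3 degrees of freedom. Power reaches 0.80 at r = 0.46 with 17 per group and at r = 0.24 with 20. At r = 0.5 with 17 per group it is 0.82.

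**The case against.** The strongest defence is that sidedness is not among the stated inputs. A null of equality can be tested against a one-sided alternative, and a one-sided 0.05 t-test with exactly the stated SD, difference and power gives 17. A reader might infer that 17 flatly contradicts the stated inputs, or that one of them was mistyped. The document supports neither: an undeclared one-sided test explains the figure without any slip, and whether 3.4 or 3.0 is a slip can be settled only from the cited trial. This part of the defence stands. It does not clear the paragraph, though. The null is framed as equality with no directional alternative, the ANOVA is non-directional, and a one-sided 0.05 test is the equivalent of two-sided 0.10, which a protocol would have to declare.

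The second defence is that these powers belong to a single unadjusted t-test, whereas the plan measures patients at baseline and three later visits. The power of the repeated measures analysis depends on within-patient correlation and could be higher. That also stands as a limit: about 70% describes the calculation as written, not demonstrably the final analysis. But the paragraph claims its 80% for a plain comparison of two groups, and it uses no correlation. If 3.4 is already the SD of a change, which the wording leaves open, the gain from baseline adjustment may not apply.

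Third, the gap at 20 per group is small: 77.6% by exact t, 79.7% by normal approximation. That is correct, and the weight of the point lies at 17.

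Two further inferences are unsupported. A reader might take the step from 20 to 17 as a planned loss, but no drop-out rate is given. A reader might also predict that a null result will be read as proof of no benefit, but the document does not discuss how such a result would be interpreted.

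**Conclusion.** The point holds in this form: the 80% power claimed for 17 per group is not met under the two-sided 0.05 test that the hypothesis and the planned analysis imply. Power is about 70% (73% by normal approximation). At 20 per group with no losses it is about 78% (79.7%), and 80% needs 22 per group (21). The figure of 17 fits the stated SD, difference and power only under a one-sided 0.05 test that the Protocol does not declare.

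This rests on reading the test as two-sided, on an SD of 3.4 and a difference of 3.0 as written, and on the unadjusted comparison that the paragraph describes. If a one-sided test was intended, the number is right, but the paragraph omits an essential input and does not match the analysis. In both cases the text has to be corrected.

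**What to change.** Keep 20 per group and correct the paragraph:

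- State that the test is two-sided at 0.05.
- Check the SD of 3.4 and the difference of 3.0 against the cited pilot trial, and say whether 3.4 is the SD of the outcome value or of a change.
- Restate the power, if both inputs are confirmed, along these lines: *With a two-sided α of 0.05 and an SD of 3.4, power for a difference of 3.0 is 70% with 17 evaluable patients per group and 78% with 20; 80% power is reached for a difference of about 3.4 with 17 per group or 3.1 with 20.*

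Optionally, base the power on a baseline-adjusted comparison of peak VO2. State as an assumption that, if 3.4 is the SD of the outcome value, a baseline–outcome correlation of about 0.46 or more brings power to 80% with 17 per group. The Protocol gives no such correlation, so this can only be conditional.

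The cost is a rewritten paragraph and a less favourable stated power. No extra patients are needed.

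### Allocation is balanced on gender because gender predicts aerobic capacity and strength, but the named ANOVA carries no gender term, which makes between-patient comparisons conservative

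*Protocol*

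**What the plan says.** Three parts of the protocol's Methods section bear on this.

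- **Allocation.** The paragraph after the sample size calculation says: "Participant stratification will be balanced for gender because men tend to have higher aerobic capacity and muscle strength than women". It continues: "The participants will be assigned randomly to a group by a computer program". The protocol itself therefore treats gender as prognostic for aerobic capacity and strength.
- **Analysis.** The paragraph on database management says: "Repeated measures ANOVA will be performed by use of SPSS statistical software in order to reveal differences between control and intervention groups". This covers the primary and secondary outcomes. It lists no between-subject factor other than group and no covariate. It also does not say whether the group main effect or the group-by-time interaction carries the comparison.
- **Visits and sizing.** The measurements are used to "evaluate the subjects at baseline at 4 weeks, 8 weeks and 5 months", so baseline is one of four occasions. The sample size is for a two-sample comparison of peak VO2 between training and control. Its inputs are a response that "within each subject group was normally distributed with standard deviation 3.4" and the condition "If the true difference in the experimental and control means is 3.0".

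**The concern.** Balancing the arms on gender means that gender can no longer contribute to the difference between arms, so the true sampling error of that difference falls. A model without gender does not know this. It leaves the gender variance in the between-patient error, and the reported standard error is larger than the true one.

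For a comparison between patients this has two effects. The test rejects a true null hypothesis less often than 5%, and part of the precision gained by balancing is not used. The trial is small, with 20 per group including a dropout allowance, so a few points of power are worth having. The outcomes concerned are those the protocol itself links to gender: aerobic capacity and muscle strength.

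**Working it through.** **The plan's own figure.** Inputs from the Methods section: difference 3.0, SD 3.4, power 0.8, alpha 0.05, 17 per group. With the exact t calculation, one-sided alpha 0.05 gives 17 per group, which reproduces the figure. Two-sided alpha 0.05 gives 22 (21 by the normal approximation). Two-sided power is 0.70 at 17 per group and 0.776 at 20 per group. The protocol does not state sidedness. That is a separate matter; the two-sided test is used below.

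**Assumptions.** The protocol gives neither a male-female gap in peak VO2 nor a share of variance, so R² (the share of the total variance due to gender) is set to 0.1, 0.2 and 0.3. Each arm has 20 analysed patients, 10 men and 10 women, and the total SD is 3.4.

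**Formulas for a comparison at one visit.**
- Implied gender gap: 2 × 3.4 × √R².
- Within-gender SD: 3.4 × √(1 − R²).
- True SE of the arm difference under exact balance: within-gender SD × √(2/20).
- Type I error of the test without gender, normal approximation: 2 × [1 − Φ(1.96/√(1 − R²))].

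Reported SEs and power come from simulation of linear models with and without gender (200,000 trials per setting, true difference 3.0 for power).

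| R² | Gap | True SE | Mean reported SE, without / with gender | Ratio | Type I error without gender | Power, without / with gender |
|---|---|---|---|---|---|---|
| 0.1 | 2.15 | 1.020 | 1.071 / 1.013 | 1.06 | 3.9% | 78.6% / 81.8% |
| 0.2 | 3.04 | 0.962 | 1.074 / 0.955 | 1.12 | 2.8% | 79.8% / 86.0% |
| 0.3 | 3.72 | 0.900 | 1.077 / 0.894 | 1.21 | 1.9% | 81.1% / 90.1% |

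Simulated type I error without gender is 3.8%, 2.9% and 1.9%, in line with the formula. With gender it is about 5% throughout. The power gain is about 3, 6 and 9 points. For smaller gaps the cost is small: the interval is about 1% wider for a gap of 1 and 5% wider for a gap of 2.

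**Repeated measures ANOVA.** Simulation with four occasions, 20 per group, assumed within-gender SD 3.0, within-person correlation 0.7 and a gender gap that is constant over time:

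| Gap | Group main effect, rejection under the null | Group-by-time, rejection under the null |
|---|---|---|
| 0 | 0.048 | 0.049 |
| 3 | 0.024 | 0.049 |
| 5 | 0.007 | 0.049 |

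The group-by-time F values are identical at all three gaps, because a constant difference in level cancels within each patient. The same holds for change from baseline.

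**With baseline as a covariate.** Take the total variance as 1 and an assumed within-gender correlation of 0.7 between baseline and follow-up, with the same gender gap at both. The overall correlation is r = 0.7(1 − R²) + R². The residual variance is 1 − r² with baseline only and (1 − R²)(1 − 0.49) with baseline and gender.
- R² = 0.1: r = 0.73; √(0.459/0.4671) = 0.991.
- R² = 0.2: r = 0.76; √(0.408/0.4224) = 0.983.
- R² = 0.3: r = 0.79; √(0.357/0.3759) = 0.975.

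Adding gender to a model that already has baseline therefore reduces the SE by only about 1% to 2.5%.

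**The case against.** The strongest objection is that the comparison most likely to carry the result is not affected. Baseline is one of the four occasions, and the objective concerns the effects of the programme over time. In that design the group-by-time term isolates the training effect, while the group main effect averages in a pre-treatment visit. The protocol's reason for balancing is a difference in level, and a constant difference in level cancels. This stands. A reader might infer that every group comparison in the trial is too imprecise, and the documents do not support that. Group-by-time would lose precision only if gender also altered the change over time, which the protocol does not say. It is also not stated whether the SD of 3.4 describes levels or changes; if it describes changes, a constant gap would not enter it.

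A second objection is that one sentence naming a method and a software package does not exclude a gender term, and that a statistical analysis plan may list it. This stands in part. The protocol is silent on gender in the model, and it would be wrong to read that as a decision to leave gender out. But it does name a method for the group comparison, and that sentence neither carries through the reason given for balancing nor says which effect is tested. Read as written, it covers between-patient comparisons, where the loss occurs.

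Third, a reader might set unadjusted power at 77.6% whatever the gender effect and conclude that all the benefit of balancing is lost. Balancing itself lowers the true sampling error, so unadjusted power rises to about 79% to 81%. The size also depends on an assumed R², on exact balance within arms and on 20 analysed per group, whereas the plan's 20 includes a dropout allowance.

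**Conclusion.** The point holds for between-patient comparisons: the ANOVA group main effect, a single-visit contrast, and the two-sample comparison of means on which the trial is sized if that is made on levels. Without gender, intervals are too wide and tests are conservative. Under the assumed 10% to 30% of variance, the SE is about 6% to 21% larger than with gender and the power forgone is about 3 to 9 points.

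It does not extend to the group-by-time test or to change from baseline when the gender difference is constant, and it nearly vanishes once baseline is a covariate. A reader might also infer that the trial's results would be biased or its false-positive rate inflated. Neither follows: the arms are balanced on gender, and the error is on the cautious side. This is a worthwhile and nearly free improvement to the analysis sentence, not a threat to validity.

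**What to change.** Amend the analysis sentence in the Methods section in three ways:

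1. Include gender, the factor on which allocation is balanced, as a between-subject factor.
2. For post-baseline comparisons, use the baseline value of the outcome as a covariate.
3. Name the effect that is tested: group-by-time, the group main effect, or the group difference at a stated visit.

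The cost is a few words and one degree of freedom per added term. Gender is already known at randomisation and baseline is already measured, so no new data are needed. If gender turns out to explain nothing, the loss is negligible: at R² = 0 and 20 per group, simulated power is 77.5% both with and without gender. For outcomes where the protocol states no link with gender, the reason to include it is that allocation was balanced on it, and little gain should be expected.
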